### 1.3 POTENTIAL RISKS TO PARTICIPANTS

We expect the proposed treatment will be safe and well tolerated. Sulfasalazine is classified as a 'category A' drug in pregnancy - it has historically been taken by large numbers of pregnant and child-bearing-aged women; and is not known to cause any increase in the frequency of direct harm, indirect harm, or anomalies in the developing fetus in either humans or animals (13). Importantly,

sulfasalazine therapy is currently continued as a treatment option for pregnant women who have concomitant rheumatoid arthritis or inflammatory bowel disease.

Possible fetal risks:

Not known to cause anomalies in/harm to the developing fetus (13).

Possible maternal risks:

Patients with preterm preeclampsia may experience discomforts or inconveniences relating to their admission to hospital, clinical examinations and blood tests, regardless of whether or not they decide to participate in the study. However, patients recruited to the study would undergo additional examinations and pathology tests that are supplementary to their routine clinical care, and as such, may experience an increase in these discomforts and inconveniences. These additional study requirements will be outlined in detail to all potential participants during the informed consent process.

Sulfasalazine is generally well-tolerated. Side effects relating to the medication can be either dose-related or idiosyncratic.

Dose-related side effects include gastrointestinal side effects (nausea, vomiting and diarrhoea), central nervous system (headache) and hematologic toxicities (including leukopenia, haemolytic anaemia and megaloblastic anaemia). Dose-related symptoms are generally experienced when taking sulfasalazine in larger doses (>4 grams per day) than we propose to administer in this study. Our participants will receive a maximum daily dose of 3 grams of sulfasalazine and will be monitored for dose-related side effects every 1-3 days by a member of the research team.

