Participants will be visited every 1-3 days from recruitment until delivery (while they remain inpatients) by a member of the research team to monitor for AEs or possible side effects of sulfasalazine, and to ensure the participant's ongoing willingness to participate in the trial. Participants who are discharged home prior to the birth of their baby will be reviewed by a researcher each time they attend their hospital for an outpatient review until they are readmitted or their baby is born. A member of the research team will be on call to attend or for advice relating to concerns raised by the participants or the clinicians providing their direct care.

Biochemical markers of preeclampsia disease (such as LFTs and proteinuria) will be monitored as a part of standard clinical care. The researchers will also have access to these routine pathology results – this data forms some of the secondary outcomes of the study.

The timing of delivery and any deviations from routine clinical care will be determined by the treating clinician or obstetric unit – not by a member of the research team. In the case where a member of the research team is also acting as the treating clinician, these decisions will be made in consultation with other members of the treating obstetric unit, with the best interests of mother and baby as the paramount consideration.

The medical histories of babies born to participants (including any pathology results from tests ordered by the treating clinicians) will be reviewed postnatally to assess for neonatal outcomes and AEs. A 'closing out' visit on the postnatal ward (or phone call following maternal discharge) will be made following the delivery of each participant's baby.

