#### **6.1.4 Supply**

The on-site hospital pharmacies will supply sulfasalazine with project funds. Upon receipt of a medication chart order/reorder of sulfasalazine for a study participant, pharmacy will dispense a suitable supply of the medication to the ward (if the participant is an inpatient) or to the participant (if an outpatient). The supply should be sufficient to last approximately five days (30 tablets). A small supply of sulfasalazine will be kept in the after-hours medication cupboard at each investigational site, in case of a participant commencing participation in the trial outside of the hospital pharmacists' normal working hours.

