#### **6.1.7 Antenatal discharge**

The majority of women enrolled in the study will likely remain as inpatients until delivery of their pregnancy. In the event that a participant is discharged home for a period of time prior to delivery, she may continue to participate in the study - a take home supply of the drug (with detailed dosage instructions) and medication diary will be arranged prior to her discharge. The medication diary will outline emergency contact details in the event of a participant experiencing an adverse event outside of the hospital. A member of the research team will meet with the discharged participant during her subsequent outpatient visits to the hospital to ensure her ongoing wellbeing while taking the study drug; assess study protocol compliance by reviewing the participant's medication diary and count the number of remaining tablets; and to arrange a further supply of sulfasalazine from pharmacy, as needed. Discharged participants will be instructed to store their sulfasalazine at <25 °C, as per the manufacturer's instructions.

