#### STUDY ASSESSMENTS – POSTNATAL

- Collection of 1 x pink-topped plasma EDTA tube (maternal blood) at delivery
- Collection of 1 x pink-topped plasma EDTA tube (cord blood)
- Collection of 6 x 30g placental samples
- Postnatal closing out visit/phone call
- Maternal and neonatal history reviews

Other information required for study assessments (such as blood test results, growth and wellbeing ultrasounds, etc.) that form a normal part of clinical care will be transcribed into the CRF from patient files.

Clinical management may vary slightly between the two participating sites or between the different obstetric units therein. A member of the research team will visit each participant every 1-3 days (or more frequently, as requested by the direct clinical care team), communicate with their clinical carers and review the participant's medical history. The researcher will update the CRF detailing:

- Any AEs experienced by the participant
- Any changes in severity of the signs or symptoms of the preeclampsia disease process
- Any pathology tests undertaken since the last study visit
- Compliance with treatment regime
- Participant wellbeing
- The participant's stated willingness to continue with the study

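### Sections 1.3 and 7 promise a side-effect check every 1-3 days for every participant, but Section 3 gives it only to inpatients and sets no maximum interval for discharged women still on drug (minor)

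*Protocol*

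**What the plan says.** Three sections of the protocol give a 1-3 day interval, and they differ in whom it covers.

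- **Section 1.3 (potential risks):** participants "will be monitored for dose-related side effects every 1-3 days by a member of the research team". This is part of the argument that drug risk is contained, and it carries no inpatient limit.
- **Section 7 (assessments):** "A member of the research team will visit each participant every 1-3 days". The CRF updates listed with it include adverse events and treatment compliance. Although the sentence sits under the postnatal heading, it plainly concerns time on treatment. It has no inpatient limit either.
- **Section 3 (design):** participants are visited "every 1-3 days from recruitment until delivery (while they remain inpatients) by a member of the research team". After antenatal discharge they "will be reviewed by a researcher each time they attend their hospital for an outpatient review until they are readmitted" or until the baby is born.

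Section 6.1.7 covers women who go home before delivery. Such a woman is given a take-home supply and a diary, and "she may continue to participate in the study". The research team meets her at outpatient visits to review the diary, count tablets and "to arrange a further supply of sulfasalazine from pharmacy, as needed". No interval is given. Section 6.1.4 sets each supply, inpatient or outpatient, at about five days (30 tablets). Section 6.1.7 also says: "The majority of women enrolled in the study will likely remain as inpatients until delivery of their pregnancy".

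**The concern.** A discharged woman on sulfasalazine is a participant on drug, so Sections 1.3 and 7 promise her a check at least every 3 days. The sections that govern her follow-up, 3 and 6.1.7, tie review to whenever she attends. Both cannot be the rule. This is a conflict between stated rules, not detail left for another document.

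Maternal adverse effects are a primary objective (Section 2.1.1). Under Section 10.2 the open-ended and specific adverse-event questions are asked at research-team contacts, so a longer gap between contacts means later prompting. Mild to moderate gastrointestinal effects are the trigger for the dose reduction in Section 6.3. A woman at home may put up with such symptoms without telephoning, so that step could also come later.

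**Working it through.** The protocol gives no figure for the interval after discharge, so there is nothing to reproduce. The check is to look for any other rule that would restore the 3-day limit.

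**1. Explicit interval after discharge.** Sections 3 and 6.1.7 give none. Table 2 (Section 7.2) lists adverse events at each later review but does not space the reviews.

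**2. Routine care rhythm.** Section 3 describes local practice as blood tests at least three times a week and CTG three times a week, with ultrasound twice weekly. Section 7 puts clinical bloods at usually every 2-3 days. Assume this rhythm continues after discharge and visits are spread evenly:

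- 3 visits in 7 days: gaps 2 + 2 + 3 = 7. Largest gap 3 days, so no shortfall.

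However, Section 3 lets the treating unit order otherwise, and Section 7 leaves the timing of bloods to the treating team. The rhythm is therefore not a research-team commitment. With fewer visits (illustrative, since the protocol gives no outpatient frequency):

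- 2 visits in 7 days: gaps 3 + 4 = 7. Largest gap 4 days, 4 - 3 = 1 day over.

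**3. Drug supply.** Section 6.1.4 gives 30 tablets. Table 1 (Section 6.3) gives 6 tablets a day at 3 g.

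- 30 / 6 = 5 days, matching the stated duration.
- 5 - 3 = 2 days over the interval in Sections 1.3 and 7.

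Because resupply is arranged at outpatient visits, this works as an indirect limit. It is a dispensing rule, not a monitoring rule, and it is longer than 3 days.

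**4. Reactive routes.** An on-call researcher (Section 3), emergency contacts in the diary (Section 6.1.7) and the instruction to report symptoms at any time (Section 10) all depend on the woman raising the matter. They cover urgent events but set no interval.

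**Size of the remedy.** If a call is made whenever 3 days pass without review, calls per gap = ceil(gap / 3) - 1:

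| Gap (days) | Calls |
|---|---|
| 2 or 3 | 0 |
| 4 | 1 |
| 5 | 1 |

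So each woman at home needs no calls at the default rhythm, one a week at two visits a week, and one per gap at a visit every five days.

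**The case against.** The strongest reply is that the specific text governs. Sections 3 and 6.1.7 deal expressly with discharged women, and a site would know what to do. On that view Sections 1.3 and 7 merely lack a qualifier, and limiting them to inpatients would end the matter. That would remove the inconsistency, but by withdrawing a safeguard that Section 1.3 relies on.

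Much of the rest of the reply stands:

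- No shortfall arises at the default rhythm, and nothing says fewer visits are expected for a woman with preterm preeclampsia at home.
- Section 10.2 does not require common gastrointestinal effects to be logged as adverse events unless serious or severe, so late prompting about these would rarely change the adverse-event count.
- Section 1.3 places dose-related symptoms generally above 4 g a day, against a maximum of 3 g here.
- The Product Information asks for blood counts and liver tests every second week early in therapy, and even a five-day gap is well inside that. It is not a symptom-check rule, however.

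Two stronger readings are tempting. A reader might infer that women at home go unmonitored or that adverse events will be missed. The documents show no such lapse, only the absence of a rule that would prevent a longer gap. A reader might also divide 30 tablets by the 4 a day of the reduced 2 g regime and infer a limit beyond five days. Section 6.1.4 sets a duration of about five days, which at 4 tablets a day is 5 x 4 = 20 tablets. The longer figure needs a dose cut after dispensing, or a fixed count of 30 whatever the dose.

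**Conclusion.** The point holds as a minor inconsistency. The textual conflict is certain: Sections 1.3 and 7 state the 1-3 day check without restriction, Section 3 restricts it to inpatients, and no maximum interval exists for discharged women on drug.

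The practical effect is conditional and small. It is nil if outpatient attendance keeps to three evenly spread visits a week. It appears only if the treating unit orders fewer, and then the supply rule indirectly limits the gap to about five days, 2 days beyond the stated interval. The consequence would be later prompted questions, and possibly a later dose reduction, in the few women sent home. Sections 3, 6.1.7 and 10 give them ways to report anything urgent.

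The number of women discharged, their time at home and their visit frequency are not in the protocol, so no trial-wide count of affected women or calls can be given.

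**What to change.** In Sections 3 and 6.1.7, add: *A discharged participant taking sulfasalazine who has not been reviewed within 3 days will be telephoned by a member of the research team and asked the questions in Section 10.2, and the contact will be recorded on the CRF.*

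In Sections 1.3 and 7, change the wording to: *visited while an inpatient, or reviewed in clinic or by phone after discharge, every 1-3 days.*

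This holds the trial to the 3-day limit it already states and makes the Section 1.3 safeguard true for every woman on drug. The cost is wording in four places and a few phone calls by the existing team, none at the default rhythm. Telephone contact is already used for closing out (Section 3). No visits, samples or analyses are added, and clinical management stays with the treating unit.

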## **4 STUDY POPULATION**

### **4.1 NUMBER OF PARTICIPANTS**

The researchers plan to recruit 20 women with preterm preeclampsia between 30+0 and 36+0 weeks gestation, over a period of 2 years. The researchers believe that this sample size is justified, as outlined in *Section 9.1* of this document.

### **4.2 INCLUSION CRITERIA**

Women who have/who are:

- A singleton pregnancy between 30+0 and 36+0 weeks at the time of treatment initiation
- Admitted as hospital inpatients with a diagnosis of preeclampsia as defined by the International Society for the Study of Hypertension in pregnancy guidelines(1)
- A pregnancy considered (by the treating obstetric unit) to be safe to continue for >12 hours after the time of recruitment
- Absence of major fetal anomalies identified on morphology ultrasound
- Aged 18-45 years at the time of recruitment
- Capable of understanding all study-related information presented to them (written, oral and electronic)
- Able to provide their written, informed consent to participate

### **4.3 EXCLUSION CRITERIA**

Women who have/who are:

- A multiple pregnancy
- Known major fetal malformation(s)
- Contraindication(s) to sulfasalazine
- Already taking sulfasalazine
- Immunodeficiency disorder(s)
- Unable to provide informed consent to participate

### **4.4 CO-ENROLMENT**

Participants will not be eligible to take part in any other intervention trials for the duration of their enrolment in this study. Participants may elect to take part in other observational research (e.g. tissue bank donations, questionnaire studies, etc.) as they wish.

## **5 PARTICIPANT SELECTION AND ENROLMENT**

### **5.1 IDENTIFYING PARTICIPANTS**

Women with a singleton pregnancy between 30+0 and 36+0 weeks gestation who are diagnosed and admitted to hospital with preeclampsia will be identified by the research team from hospital admission data sources or referred by clinical staff (in Birthing Suites, Emergency, Antenatal Clinic and the Fetal Monitoring/Pregnancy Day Stay Units) to the research team.

### **5.2 CONSENTING PARTICIPANTS**

Eligible participants will be identified by their clinical care team and referred to the research team or identified by the researchers from hospital admission data. A member of the research team will approach potential participants and provide them with a verbal explanation of the study, as well as a written or electronic copy of the *Patient Information and Consent Form* (PICF). All eligible women will have the opportunity to discuss and ask questions about the study with a member of the research team who is also an obstetrician or obstetric trainee prior to consenting. Informed, written consent will only be collected once the patient has had adequate time to read and reflect upon the study information and had all questions answered to her satisfaction. Recruited participants will retain their copy of the PICF and be given a copy of their signed consent form for their personal records.

### **5.3 SCREENING FOR ELIGIBILITY**

To be eligible for the study, a woman must have a singleton pregnancy between 30+0 and 36+0 weeks gestation, with a pending or current inpatient admission for a diagnosis of preeclampsia according to the Society for the Study of Hypertension in pregnancy guideline(1). Additionally, the woman must be aged 18-45 years; capable of understanding the study information presented to her; have the ability to provide written consent; considered by the treating obstetric team to be safe to continue the pregnancy for >12 hours; and have a normal fetal morphology scan/aneuploidy testing result(s) (if performed) for this pregnancy. These parameters will be applied to determine eligibility for the study for all women referred to or identified by the research team. Eligibility (or non-eligibility) will be documented by a member of the research team in the medical history of all patients screened for inclusion in the study.

### **5.4 INELIGIBLE AND NON-RECRUITED PARTICIPANTS**

No further information will be collected on women once they are deemed to be ineligible to participate in the study, or once they decline or withdraw consent for their inclusion. Anonymised information will be collected on a password protected, online screening log to capture all patients assessed for their eligibility, whether or not they are recruited. Those women who are not recruited

into the study or who withdraw their consent to participate will continue with standard clinical care for the treatment of their preeclampsia, as per their treating hospital's SOP and treating obstetric unit instruction.

## **5.5 RANDOMISATION**

Not applicable – this is a single arm, unblinded study.

### **5.5.1 Treatment Allocation**

Not applicable.

### **5.5.2 Emergency Unblinding Procedures**

Not applicable.

## **5.6 WITHDRAWAL OF STUDY PARTICIPANTS**

Participation in the study is completely voluntary. Participants will be made aware of their ongoing right to discontinue taking sulfasalazine or to withdraw entirely from the study at any time, and for any reason. The research team also retains the right to discontinue a participant from taking sulfasalazine and initiating their withdrawal from the study at any time, if it is deemed by a Principal Investigator or Site Leader to be in the patient's and/or her baby's best interest(s).

If a participant is withdrawn from the study by a researcher due to a *Serious Adverse Event* (SAE), the relevant hospital Site Leader will arrange for medical follow-up visits or other contact with the treating hospital until the event has been resolved or stabilised. Any data collected from the participant up until their removal from the study will still be used in statistical analyses, unless this is specifically refused by the participant.

If a participant withdraws their consent to the study at any point, no further data will be collected about them by the research team. However, permission will be sought to continue using anonymised data and research samples collected from the participant up until the point of withdrawal. The research team will attempt to identify with the participant the reason/s for their withdrawal, in case a study protocol amendment and/or medical follow-up visits are warranted.

The research team will make reasonable attempts (i.e. attempting to make contact on  $\geq 3$  occasions, using more than one mode of communication) to locate a participant before they are deemed to be 'lost to follow-up'. If a participant is deemed to be lost to follow-up, but has not indicated to the research team that they wish to be withdrawn from the study, their anonymised data and any collected samples will still be used in the final analysis.

## **6 INVESTIGATIONAL MEDICINAL PRODUCT**

### **6.1 STUDY DRUG**

Generic: Sulfasalazine

Traded as: Salazopyrin EN (Pfizer Australia Pty. Ltd.)

#### **6.1.1 Study drug identification**

Salazopyrin EN (sulfasalazine) enteric coated – *Australian Register of Therapeutic Goods* (ARTG) ID 14485 – supplied in bottles of 100 x 500 mg tablets.

Physical description: Elliptical convex, yellow-orange, enteric coated tablets marked with *KPh* on one side; *102* on the reverse.

#### **6.1.4 Supply**

The on-site hospital pharmacies will supply sulfasalazine with project funds. Upon receipt of a medication chart order/reorder of sulfasalazine for a study participant, pharmacy will dispense a suitable supply of the medication to the ward (if the participant is an inpatient) or to the participant (if an outpatient). The supply should be sufficient to last approximately five days (30 tablets). A small supply of sulfasalazine will be kept in the after-hours medication cupboard at each investigational site, in case of a participant commencing participation in the trial outside of the hospital pharmacists' normal working hours.

#### **6.1.5 Labelling and packaging**

Sulfasalazine will be supplied to the admitting ward for each individual participant by the hospital pharmacies in accordance with local SOPs for prescription study medication labelling and packaging. As this is not a blinded study, sulfasalazine can still be identified by its generic name, trade name and dose on the packaging/label.

#### **6.1.6 Storage**

Sulfasalazine will be securely stored in the hospital pharmacies, and will be dispensed to the admitting wards for specific trial participants or to the participant themselves upon receipt of an inpatient medication chart or prescription. Tablets will be kept secure on the wards in locked medication drawers or rooms, as per the local hospital SOP for the safe storage and management of prescription medications. While tablets remain in the hospital, they will be kept at room temperature (<25 °C), as per the manufacturer's guidelines (see *Appendix 1*). Upon delivery of a participant's baby or at their withdrawal from the study, unused tablets will be returned to the hospital pharmacy.

#### **6.1.7 Antenatal discharge**

The majority of women enrolled in the study will likely remain as inpatients until delivery of their pregnancy. In the event that a participant is discharged home for a period of time prior to delivery, she may continue to participate in the study - a take home supply of the drug (with detailed dosage instructions) and medication diary will be arranged prior to her discharge. The medication diary will outline emergency contact details in the event of a participant experiencing an adverse event outside of the hospital. A member of the research team will meet with the discharged participant during her subsequent outpatient visits to the hospital to ensure her ongoing wellbeing while taking the study drug; assess study protocol compliance by reviewing the participant's medication diary and count the number of remaining tablets; and to arrange a further supply of sulfasalazine from pharmacy, as needed. Discharged participants will be instructed to store their sulfasalazine at <25 °C, as per the manufacturer's instructions.

